### Trial design

#### Study design

This is a non-inferiority, multicentre, randomized, open label study on 4 antimalarial treatments, namely DHA-PQ, MQAS, AQAS and AL, assessed in each site using a “balanced incomplete block design” – with 3 out of 4 arms used in each site. There are 7 sites in the study distributed in the four countries, i.e. Burkina Faso (Nanoro and Nazoanga), Ghana (Effiduase, Ejisu and Juaben), Malawi (Chikwawa) and Zambia (Nchelenge).

The treatments tested are distributed in a way to allow a head-to-head comparison and the establishment of the treatment’s relative value according to a series of outcomes (Table 1). This approach has the advantage of testing several treatment options at the same time, maximizing the use of resources, and is the most likely to achieve our aim of identifying at least 2 antimalarial treatments suitable for use in pregnancy and one rescue/alternative treatment.

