***Eastern-Southern Africa: comparator AL***			
Malawi (870)	DHA-PQ (290)	AL (290)	AQAS (290)
Zambia (870)	MQAS (290)	DHA-PQ (290)	AL (290)

AQAS: amodiaquine-artesunate; DHA-PQ: dihydroartemisinin-piperaquine; AL: artemether-lumefantrine; MQAS: Mefloquine-artesunate.

The primary analysis is the assessment of therapeutic equivalence of the 4 treatments (clinical non-inferiority) with respect to therapeutic success at day 63 and their safety throughout the follow up, i.e. up to one year after delivery.

The following procedures are used to ensure an unbiased assignment of treatment safety and efficacy:The randomization list is generated prior to the beginning of the study.The interpretation of the PCR reading is blinded or masked with regard to the treatment allocation of the patients.An independent Data Safety and Monitoring Board (DSMB) reviews all safety data.

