#### Primary endpoint

There are two primary end points:**Treatment Failure** (TF) (PCR adjusted) at day 63 defined according to the WHO criteria [14] as the sum of early and late treatment failures. Early Treatment Failure (ETF) could be one of the following: Development of danger signs or severe malaria on Day 0, Day 1, Day 2 or Day 3, in the presence of parasitaemia; Parasite density on Day 2 > Day 0 count, irrespective of axillary temperature; Presence of parasitaemia on Day 3 with fever (axillary temperature ≥ 37.5°C); Parasitaemia on Day 3 ≥ 25% of count on Day 0. Late treatment failure (LTF) is divided in late clinical and late parasitological failure. Late Clinical Failure (LCF): Development of danger signs or severe malaria on any day after Day 3 in the presence of parasitaemia, without previously meeting any of the criteria of Early Treatment Failure; Presence of parasitaemia and fever on any day after Day 3, without having previously meet the criteria of ETF. Late Parasitological Failure (LPF): Presence of parasitaemia on any day from day 7 onwards and axillary temperature <37.5°C, without previously meeting any of the criteria of ETF or LCF. The Adequate Clinical and Parasitological Response (ACPR) is 1-TF. It is defined as absence of parasitaemia at the end of the follow up period, irrespective of axillary temperature without previously meeting any of the criteria of early and late treatment failure. In the adjusted estimates, patients with late asexual parasite reappearance (with or without fever) are considered ACPR if the PCR analysis shows a new infection rather than a recrudescence.**Safety profiles** including significant changes in relevant laboratory values. Subjects are monitored for 63 days for possible development of adverse events. All adverse events are recorded on the specific form in the electronic CRF. Vital signs, blood chemistry and haematology are monitored and changes in relevant laboratory parameters are assessed.

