##### Safety

For safety analysis, all non-serious and serious adverse events (SAE) are grouped according to a pre-specified side-effect coding system and tabulated. The number (and percentage) of patients experiencing any adverse event, any SAE, and any drug-related SAE are compared between treatment groups using Fisher's exact test. Safety is analyzed using the all-patients-treated approach.

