#### Safety variables

Safety is closely monitored during the course of the study in compliance with ICH/GCP guidelines. At each visit, the investigator ascertains the occurrence of any adverse events since the previous visit; including those involving laboratory values which are out of normal range and are of clinical importance to be considered as AEs, and the proper AE reporting procedure is followed. The severity of a clinical adverse event is scored according to the following scale: mild, moderate, severe and life-threatening.

Serious Adverse Events (SAEs) are defined as any untoward medical occurrence that, at any dose of the medication given, fulfilled the following criteria; death, life-threatening, requiring hospitalization or prolongation of hospitalization, resulting in persistent or significant disability or incapacity, congenital anomaly/ birth defect, or other situations such as important medical events that may not be immediately life-threatening or result in death or hospitalization but may jeopardize the subject or may require medical or surgical intervention to prevent one of the other outcomes listed in the above definition. The reporting investigator assesses the relationship between investigational product and the occurrence of each AE/SAE. The relationship of an adverse event to study drug is assessed according to the following definitions: ‘Definitely unrelated’, ‘Unlikely’, ‘Possible’, ‘Probable’ and ‘Definitely related’. The outcome of each AE is assessed according to the classification as follows – ‘Completely recovered’, ‘Not yet completely recovered’, ‘Deterioration’, ‘Permanent damage’, ‘Death’, ‘Ongoing’ and ‘Unknown’.

Each SAE has to be reported to the sponsor and to the concerned ethical bodies in the study countries within 24 working hours since the time the study staff becomes aware of it, and any reporting delay has to be explained. All the SAE forms are further sent by the sponsor to the concerned ethical bodies in Belgium and to the independent DSMB. Each SAE is followed up until resolution.

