In the second and third trimester of pregnancy, WHO recommends the use of ACT known to be effective in the country/region. Despite this recommendation, it should be recognised that the available information on the treatments to be used in this trial is limited. ACT should not be used in the first trimester of pregnancy, the time of greatest concern for potential teratogenicity, and particular care will be taken in excluding women of this gestational age. DHA-PQ is the least used of the 4 ACTs studied in this trial and it is not among the WHO recommended ACTs during pregnancy because of insufficient information [3]. However, DHA-PQ is the first line treatment in Papua Indonesia, where it is also used to treat pregnant women with malaria; an observational study reported significant benefits of DHA-PQ over quinine-based regimens in reducing recurrent malaria and poor foetal outcome in pregnant women in the second or third trimester [26]. This trial will increase significantly the knowledge on the use of DHA-PQ in African pregnant women.

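### Investigator-attributed drug-related SAEs are tested between open-label arms, so a difference in suspicion can appear as, or hide, a safety difference in that one of three comparisons

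*Protocol article*

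**What the plan says.** Four statements in the protocol article bear on this.

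- **Masking.** Study design: "This is a non-inferiority, multicentre, randomized, open label study on 4 antimalarial treatments". The list of bias-control procedures after Table 1 names one masked step: "The interpretation of the PCR reading is blinded or masked with regard to the treatment allocation of the patients". It also provides for an independent DSMB to review the safety data, but does not describe that review as masked or as adjudication of causality.
- **Who decides relatedness.** Safety variables: "The reporting investigator assesses the relationship between investigational product and the occurrence of each AE/SAE". The judgement is made on a five-level scale from definitely unrelated to definitely related.
- **What is done with it.** Statistical analysis, Safety: women with any adverse event, with any SAE and with "any drug-related SAE are compared between treatment groups" by Fisher's exact test, in all treated patients.
- **Status.** Primary endpoint: "There are two primary end points". The second is the safety profile, which also covers laboratory values and vital signs.

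**The concern.** Randomisation makes the arms comparable, so a comparison of all SAEs needs no case-by-case opinion on cause. Once events are filtered through the opinion of someone who knows the drug, the count compared is the SAE risk multiplied by the share that this person calls related. Randomisation balances only the first factor. The second can differ between drugs with no difference in harm.

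There is reason to think suspicion might differ. The Discussion says "DHA-PQ is the least used of the 4 ACTs studied in this trial" and notes that it lacks a WHO recommendation in pregnancy for want of information. The amendment history records manufacturer signals for the amodiaquine, piperaquine and mefloquine combinations, and none for artemether-lumefantrine.

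At stake is a statement about drug-related SAEs in a trial meant to inform treatment guidelines. A significant excess could reflect suspicion alone. Equally, a real excess for a trusted drug could disappear: twice the SAE risk with half the attribution share gives the same expected count.

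**Working it through.** **The plan's own figures.** The concern disputes no number in the plan. The sample size only supplies the arm size: about 700 evaluable and 870 recruited per arm. Inflating for loss gives 700 / (1 − 0.20) = 875, close to the stated 870. Because safety uses all treated patients, 870 is used below.

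**Assumptions.** The documents give none of the following:
- true SAE risk *r*, the same in both arms: 1%, 3% or 5%;
- share of SAEs called related, *a*₁ and *a*₂: 20% in one arm, 20% to 50% in the other;
- a two-sided 0.05 level, applied to one pair of arms. The Safety text states no level and does not say whether the tests are pair-wise.

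**Method.** The number of women with a drug-related SAE in arm *i* is Binomial(870, *r* × *a*ᵢ). The chance of a significant result is the sum of Bin(x; 870, *r a*₁) × Bin(y; 870, *r a*₂) over all pairs (x, y) for which Fisher's exact *p* is below 0.05. This is exact enumeration, not simulation.

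**Expected counts at *r* = 3%.** 870 × 0.03 = 26.1 women with an SAE per arm. At 20% attribution, 26.1 × 0.20 = 5.2 are labelled related; at 50%, 26.1 × 0.50 = 13.1.

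**Results, with no true difference in SAE risk.**

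| Attribution | SAE risk | Fisher significant |
|---|---|---|
| 20% v 20% | 3% | 2.2% |
| 20% v 30% | 1% | 1.1% |
| 20% v 30% | 3% | 6.5% |
| 20% v 30% | 5% | 10.5% |
| 20% v 40% | 3% | 18.6% |
| 20% v 50% | 3% | 36.8% |
| 20% v 50% | 5% | 60.8% |

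Where attribution is rare in both arms the effect nearly vanishes: 5% v 10% gives 1.6% at *r* = 3% and 5.4% at *r* = 5%.

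**One concrete data set.** Suppose 26 women have an SAE in each arm of 870, of whom 5 and 15 are labelled related. Fisher's test on the related counts gives *p* = 0.040. On all SAEs, 26 v 26, it gives *p* = 1. The same table would then carry two contradictory messages, and only the labelled one would be significant.

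**The case against.** The strongest reply has four parts.

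1. **The sound comparison is already planned.** Any adverse event and any SAE are tested in the same sentence, on the same patients, without the causality label. A reader would see 26 v 26 beside 5 v 15. This stands, and it confines the problem to one of three comparisons.
2. **No decision depends on the test.** The margin and decision rule in the Efficacy section apply to response rates only. Safety has no stated level, margin or rule. This also stands, so the percentages above describe how often a misleading p-value would be printed, not how often a formal wrong decision would be made.
3. **The size depends on chosen inputs.** Large figures need large attribution gaps, and modest gaps or few SAEs keep the rate near or below 5%. This stands, which is why a range is given.
4. **Safeguards may exist elsewhere.** The DSMB receives the SAE forms, and investigator causality is a routine safety item. That supports collecting and showing the judgement. It does not make the judgement masked, and the test itself is stated in the text rather than left to another document. On this part the objection fails.

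A reader might infer from the Discussion and the amendments that DHA-PQ in particular will be over-attributed. The documents do not support that. They report signals for three of the four combinations, call information on all the treatments limited, and also cite favourable experience with DHA-PQ in pregnancy. They contain no evidence of unequal attribution, so neither its presence nor its direction can be asserted.

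**Conclusion.** The point holds within limits. A stated between-arm test, belonging to a primary endpoint, uses an outcome that an unmasked investigator defines, and nothing in the text protects that step. The test therefore cannot separate a difference in harm from a difference in suspicion.

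Its size is unknown, because it depends on SAE risk and attribution shares that the documents do not give. Under the assumptions listed, the chance of a significant result with no true difference goes from about 2% with equal attribution (20%, SAE risk 3%) to 6.5%, 19% and 37% as the second arm's share rises to 30%, 40% and 50%. Across the SAE risks tried, the 20%-based contrasts range from about 1% to 61%.

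A reader might conclude that the primary safety analysis as a whole is invalid. That goes too far. The any-AE and any-SAE comparisons do not depend on the causality label, the safety endpoint is broader than SAEs, and no conclusion of the trial is tied by rule to the drug-related test.

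**What to change.** In the Safety part of the statistical analysis:
- remove drug-related SAEs from the outcomes compared by Fisher's exact test;
- state that the between-arm conclusion on SAEs rests on any SAE regardless of attribution, which is already planned;
- report investigator-attributed SAEs by arm as counts and percentages, without a p-value, and say that attribution was made with knowledge of the treatment.

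The cost is one phrase in the analysis text. No data are lost, and sample size, data collection and safety reporting are unchanged. Data collection has finished, so the change should be fixed before the comparative safety analysis is run.

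Masked re-classification of events by the DSMB is not needed for this. It would add a procedure beyond the role that the article gives the board, whereas dropping the test removes the problem at no cost.

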#### Selection of the patients

All pregnant women in the second and third trimester (<37 weeks) and attending the antenatal clinic of the study health facilities are systematically screened for malaria infection with a rapid diagnostic test; if positive they are further assessed for eligibility. They are included if they are at least 15 years old, with a pregnancy of at least 16 weeks, a *P. falciparum* monoinfection of any density, regardless of symptoms, and a Hb concentration of at least 7 g/dL. Pregnant women with a negative blood slide are not included in the study and go through the routine antenatal clinic procedures according to national policy and receive a dose of sulfadoxine-pyrimethamine (SP) as intermittent preventive treatment (IPT). Exclusion criteria include history of allergic reactions to the study drugs, of known pregnancy complications or bad obstetric history such as repeated stillbirths or eclampsia, of presence or history of major illnesses likely to influence pregnancy outcome, e.g. diabetes mellitus, severe renal or heart disease, or active tuberculosis, current cotrimoxazole prophylaxis or ARV treatment. Table 2 provides the full list of inclusion/exclusion criteria. The reason of including women with any parasite density is justified by the important adverse outcomes any malaria infection has on the mother’s and her offspring’s heath. Limiting the inclusion to women at 16 weeks or more of gestation is justified by the uncertainty on the safety of ACT when administered during the first trimester of pregnancy. The gestational age was confirmed by measuring symphysio-fundal height and the foetal viability by using an ultra-sonography. Exclusion criteria are formulated because of possible safety issues, e.g. history of allergic reactions to the study drugs, or the need for a clear interpretation of the therapeutic response, e.g. recent exposure to antimalarial treatments.

**Table 2 Tab2:** **Inclusion and exclusion criteria**

Inclusion criteria	Patients eligible for inclusion in the trial must fulfil all of the following criteria
	Gestation ≥16 weeks and <37 weeks;
	*P. falciparum* monoinfection of any density, with or without symptoms
	Hb ≥ 7 g/dL;
	At least 15 years old;
	Residence within the health facility catchment’s area;
	Willing to deliver at the health facility;
	Willing to adhere to the study requirements (including, in Zambia and Malawi, HIV VCT)
	Ability to provide written informed consent; if the woman is minor of age/not emancipated, the consent must be given by a parent or legal guardian according to national law (however, in this case, the investigator is responsible to check that the woman herself is also freely willing to take part in the study).
**Exclusion criteria**	**Patients who meet any of the following criteria are not eligible for the study**
	History of allergic reactions to the study drugs;
	History of known pregnancy complications or bad obstetric history such as repeated stillbirths or eclampsia;
	History or presence of major illnesses likely to influence pregnancy outcome including diabetes mellitus, severe renal or heart disease, or active tuberculosis;
	Current cotrimoxazole prophylaxis or ARV treatment;
	Any significant illness at the time of screening that requires hospitalization, including severe malaria;
	Intent to move out of the study catchment area before delivery or deliver at relative’s home out of the catchment area.
	Prior enrollment in the study or concurrent enrollment in another study.
	Unable to take oral medication
	Clear evidence of recent (1 week) treatment with antimalarials or antimicrobials with antimalarial activity (clindamycin; azythromycin; etc.)

##### Informed consent

For the informed consent, all interviews are conducted in the native language of the patients by a qualified person identified by the Investigator. Written information and consent forms in the local language are provided to the women or Legally Authorized Representatives (LAR) for their review. After the interview, the patients and, in case they are of minor age/not emancipated, the parents or guardians are asked to confirm their willingness to participate in the study by signing (or thumb-printing if illiterate) the consent form.

Each eligible pregnant woman who agrees to give informed consent is assigned a unique study number and enrolled. Besides malaria infection and parasite density, Hb, total white blood cell count, differential count, total bilirubin, ALAT and creatinine are measured. In addition, a blood sample is collected on filter paper for later genotyping.

#### Randomization and treatment

Randomisation is carried out according to a pre-established list comprising blocks of varying size and stratified according to the number of recruitment points in each site. Allocation of treatment according to the randomization list is in sealed envelopes labelled with the patient’s unique code, guaranteeing concealment until recruitment**.**

The study treatment is administered during the first 3 study days (days 0–2) by the study doctor or nurse and the patient kept for one hour in the clinic. If vomiting occurs within 30 minutes, a full treatment is re-administered, half a dose if after 30 minutes. In case of persisting vomiting, an alternative treatment, e.g. quinine, is provided.

#### Patients follow up

Scheduled visits are at day 3, 7 and then every week until day 63 post-treatment. However, women are encouraged to attend the antenatal clinic if they felt ill between scheduled visits. At the end of the active follow-up period, women are asked to attend the antenatal clinic monthly and at any time they feel unhealthy until delivery. At each visit, scheduled and unscheduled, the medical history since the last visit (including any treatment taken), current signs and symptoms (if any) are collected. A blood sample for thick and thin blood film and later genotyping to determine the rate of re-infection is collected and the body temperature checked. Haematology (Hb, total white blood cell count, differential count) is measured at day 7, 14, 28 and 63; biochemistry (total bilirubin, ALAT and creatinine) at day 7 and 14.

If pregnant women recruited during the third trimester deliver before the end of the 63-day active follow, scheduled visits continue after delivery until the day 63 is completed. The outcome of pregnancy, including any congenital abnormality, the birth weight and maternal Hb are collected as soon as possible after delivery. In addition, a placenta impression smear and a placenta biopsy for later histopathological analysis are collected. Both the mother and the new-born are reassessed twice after delivery for any adverse event: between 4 and 6 weeks and then after one year (Table 3). Antimalarials or antibiotics with antimalarial activity (erythromycin or other macrolides, co-trimoxazole or other sulphonamides, any tetracycline including doxycycline, and quinolones, clindamycin) cannot be administered during the active follow up as it would lead to withdrawal of the patient from the study.

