#### Statistical analysis

A detailed analysis plan is drawn up prior to the analysis.**Baseline comparability**: Patients in each treatment group in each site are described separately with respect to baseline characteristics. The clinical importance of any imbalance will be noted, though statistical tests of significance are not undertaken.**Primary analyses**: The primary analysis of the study is the assessment of therapeutic equivalence of the 4 treatments (clinical non-inferiority) with respect to therapeutic success at day 63 and their safety throughout the follow-up, i.e. up to one year after delivery.

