##### Efficacy

Therapeutic equivalence is assessed using the pair-wise difference in response rates (percentage of women with therapeutic success). Assessment of the difference in true response rates is performed by calculating the two-sided 95% confidence interval for the difference in response rates from the observed data, using the following decision rule:

if the two-sided 95% confidence interval for the difference in response rates lies entirely between −5% and +5%, then therapeutic equivalence of the two treatments is concluded;if the 95% confidence interval for the difference in response rates includes −5% or +5%, then therapeutic equivalence cannot be established;if the 95% confidence interval for the difference in response rates lies entirely below −5% or entirely above 5%, then one treatment is clinically inferior to the other.

The primary analysis uses the combined data from all 4 centres together, with adjustment for any centre effects, using an additive model for the response rates (i.e. a generalized linear model with Bernoulli error distribution and an identity link function). This allows the assessment of all 6 possible pair-wise treatment comparisons using all available data. Equivalence will be established using two-sided confidence intervals. Though 6 treatment comparisons will be performed, no adjustment for multiplicity is needed as the focus of the study is on the individual pair-wise treatment comparisons. In addition, combined hypotheses of interest (e.g. all 4 treatments are therapeutically equivalent) require each of the individual hypotheses to be accepted. Consequently, there is no inflation of the type I error rate due to multiple testing. However, the power for combined hypotheses is lower than for the individual pair-wise comparisons. Thus, the power calculation of this study required a high (95%) power for individual pair-wise treatment comparisons, resulting in an acceptable (80%) power for the combined hypothesis. For the efficacy analysis, both an intention-to-treat and a per-protocol approach are adopted, with the per-protocol analysis being the primary approach, as recommended for equivalence studies.

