**Table 3 Tab3:** **Study procedures/study visit schedule**

Day	0	1	2	3	7	14	21	28	35	42	49	56	63	Any other day ^1^	Delivery	4-6 weeks post-partum	EPI clinics	1 year post-partum
History (symptoms)	X																	
Informed consent	X																	
Examination (clinical)	X	X	X	X	X	X	X	X	X	X	X	X	X	X	X			
Foetal viability	X			X	X	X	X	X	X	X	X	X	X	X				
Blood Pressure	X	X	X	X	X	X	X	X	X	X	X	X	X	X	X			
Temperature	X	X	X	X	X	X	X	X	X	X	X	X	X	X	X			
Blood film	X	X	X	X	X	X	X	X	X	X	X	X	X	X	X			
Filter paper PCR	X				X	X	X	X	X	X	X	X	X	X	*X* ^2^			
Adverse events	X	X	X	X	X	X	X	X	X	X	X	X	X	X	X			
Concomitant medications	X	X	X	X	X	X	X	X	X	X	X	X	X	X	X	X		
Hb	X				X	X		X		X			X		X			
Haematology	X				X	X		X					X		X			
Treatment	X	X	X															
Blood sample for PK					X													
Pop PK	3 samples/woman according to a predefined schedule (120 women in 3 sites each)																	
*In vitro* test	X	and time of recurrent infection																
Biochemistry	X				X	X		X^3^					X^4^					
Placenta sample															X			
New born assessment															X	X		
Infant assessment																	X	X

^1^Spontaneous attendance to the health facility.

^2^Includes placental blood sample.

^3^Only ALAT and total bilirubin.

^4^Only ALAT and total bilirubin, and only if abnormal at Day 28.

Patients with treatment failure, including parasitological failure, are treated with rescue treatment (quinine 10 mg/kg orally three times a day for 7 days or an anti-malarial treatment according to the country’s national guidelines) and their active follow up stopped. Nevertheless, they are still followed up (safety data) until one year post-delivery.

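### A prohibited antimalarial or antibiotic leads to withdrawal from the study, without the continued safety follow-up that the protocol gives to treatment failures

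*Protocol article*

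**What the plan says.** Three places in the Protocol article deal with women who receive another antimalarial or a drug with antimalarial activity after enrolment.

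- **Patients follow up.** The section lists macrolides, co-trimoxazole and other sulphonamides, tetracyclines, quinolones and clindamycin, besides antimalarials. These "cannot be administered during the active follow up as it would lead to withdrawal of the patient from the study".
- **Text after Table 3.** Women with treatment failure, including parasitological failure, receive quinine "or an anti-malarial treatment according to the country’s national guidelines) and their active follow up stopped". The next sentence retains them: "Nevertheless, they are still followed up (safety data) until one year post-delivery".
- **Randomization and treatment.** "In case of persisting vomiting, an alternative treatment, e.g. quinine, is provided". Whether such a woman stays in follow-up is not said.

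The analyses that need the later data are these. Safety is one of two primary endpoints: "Subjects are monitored for 63 days for possible development of adverse events". The primary analysis under Statistical analysis covers the treatments and "their safety throughout the follow-up, i.e. up to one year after delivery". Under Safety, "Safety is analyzed using the all-patients-treated approach". Under Efficacy, "both an intention-to-treat and a per-protocol approach are adopted", with per-protocol as the primary approach. Mean birth weight, low birth weight and placental infection are secondary endpoints.

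**The concern.** A drug with antimalarial activity confounds the parasitological outcome at day 63. That is a reason to stop evaluating efficacy. It is no reason to stop recording adverse events, delivery, birth weight or the infant's condition. The protocol draws this distinction for treatment failures but not for other women given a listed drug.

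At stake is the completeness of a primary endpoint and of the birth outcomes. The women affected are selected by something that happens after randomisation, namely receipt of a listed drug. That is often, though not always, a response to illness. Staff who prescribe know the arm, so the frequency of and reasons for such use could differ between arms. HIV-infected women are one group to whom this could apply. They may enrol if not currently on co-trimoxazole or antiretrovirals, and one who starts co-trimoxazole within the 63 days would meet the rule.

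**Working it through.** **1. The two rules side by side**

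| | Treatment failure given rescue (text after Table 3) | Listed drug given otherwise (Patients follow up) |
|---|---|---|
| What ends | Active follow-up | Participation in the study |
| Safety follow-up to one year after delivery | Stated to continue | No statement |

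Both groups receive a drug with antimalarial activity. The prohibition itself uses the narrower term, active follow-up, for the period in which it applies, and then names the study as what the woman leaves. A site reading both passages would reasonably take them as two different consequences.

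**2. What the literal rule would lose**

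Table 3 schedules adverse-event recording to delivery, newborn assessment at delivery and at 4 to 6 weeks, and infant assessment at EPI clinics and at one year. A woman withdrawn before day 63 would contribute none of these from then on. Her adverse-event record is cut short whether the safety horizon is 63 days or one year after delivery.

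**3. How many women**

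The document gives no rate of listed-drug use, so the following rates are assumptions. Inputs from Sample size: 870 women per treatment, and 4 × 870 = 3,480 in total.

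| Assumed use | Per treatment (870 × rate) | Total (3,480 × rate) |
|---|---|---|
| 2% | 17.4 | about 70 |
| 5% | 43.5 | 174 |
| 10% | 87 | 348 |

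**4. Is it a matter of power?**

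First the plan's own figure: 700 / (1 − 0.20) = 875, against the stated 870, which agrees within rounding.

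The approximate power of one pairwise equivalence comparison, with true success of 95% in both arms and a margin of 5 points, is

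2Φ(0.05/SE − 1.96) − 1, with SE = √[2 × 0.95 × 0.05 / (n × 8/9)].

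The factor 8/9 is the efficiency of the incomplete block design: four treatments, three per country, each pair meeting in two countries, so (2 × 4)/(3 × 3).

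| Loss | Evaluable n per treatment | Power |
|---|---|---|
| 20% as planned | 870 × 0.80 = 696 | 96.2% |
| 5% on top | 870 × 0.75 = 652.5 | 94.8% |
| 10% on top | 870 × 0.70 = 609 | 93.0% |

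The required power is 95%. Even if these withdrawals came wholly on top of the planned loss, efficacy power would hardly move. The issue is selective missing safety and birth data, not sample size.

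**The case against.** The strongest reply is that the loss is inferred. No sentence says that safety or delivery follow-up ends for these women. The withdrawal wording is a reason attached to a prohibition, not a withdrawal procedure, and may be loose phrasing for the end of active follow-up. The article also condenses a fuller protocol, where procedures after withdrawal would normally stand. This holds as far as it goes: what sites actually did cannot be known from this text. But the point is not that a procedure is missing. The article states a consequence, and that consequence differs from the one it states for treatment failures. If the narrower meaning was intended, the wording still needs correcting.

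Several stronger readings are tempting and are not supported:

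- **That the rule removes women from the intention-to-treat and all-patients-treated sets.** The Efficacy and Safety sections exclude nobody for withdrawal. A treated woman stays in the set with her data to that point; only later outcomes are missing.
- **That data are lost in women who fell ill.** The trigger is a drug, which may be preventive, as with co-trimoxazole prophylaxis. Women with treatment failure are expressly kept.
- **That a large share of serious events would be missed.** Assume a 3% event rate, 10% withdrawn and three times the risk in them. Then 0.9r + 0.1 × 3r = 0.03 gives r = 2.5%, with 7.5% in the withdrawn, so 87 × 0.075 = 6.5 of 26.1 events per treatment, or 25%. All three inputs are assumed. The figure is also an upper bound, because it counts every event as lost. Events before withdrawal are recorded, and Safety variables requires each known serious event to be followed to resolution.
- **That the safety comparison is biased.** Unequal loss between arms is plausible in an open-label trial, but nothing in the document shows it.

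The 20% allowance for loss to follow-up may already cover some of these women. It protects the number of evaluable women and does nothing about which women are missing.

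**Conclusion.** The concern holds in limited form. The protocol prescribes withdrawal from the study for a listed drug and does not extend to these women the safety follow-up that it keeps for treatment failures. Read as written, this sits badly with a primary safety analysis of all treated women to one year after delivery, and with the birth-weight endpoint. Later adverse events, delivery, birth-weight and infant data would be missing for women given a listed drug other than as rescue. The missingness may be informative. Its size is unknown: about 70 to 348 of 3,480 women, if use is 2% to 10%, and only if sites applied the literal rule. The effect on efficacy power is minor. This should be corrected, but it does not by itself invalidate the trial.

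**What to change.** **Wording.** Reconcile Patients follow up with the text after Table 3. A prohibited drug should end the efficacy evaluation only: the woman leaves the per-protocol set, and the plan states how she counts in the intention-to-treat analysis at day 63. Calling her censored is not enough, because the primary model is a Bernoulli identity-link model of day-63 success and has no place for a censoring date. Mother and infant stay in safety, delivery, birth-weight and one-year follow-up. The follow-up status of a woman given alternative treatment for persisting vomiting should be stated in the same place.

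**Reporting.** Trial status says that data collection is complete, so a change of wording cannot recover missed visits. The sponsor should state what was done in practice and report any women withdrawn under this rule by arm and reason. All their available data, including any delivery and infant data obtained, should stay in the all-patients-treated analysis. If the numbers are not trivial, a sensitivity analysis of the safety and birth outcomes should be added.

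**Cost.** For a trial still recruiting, this would be a one-sentence amendment and a little extra follow-up work, since the visits are already scheduled. Here it is a clarification and one table. It concerns data collection only; no view is taken on which drugs may be given.
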